# ALIMUS—We are feeding! Study protocol of a multi-center, cluster-randomized controlled trial on the effects of a home garden and nutrition counseling intervention to reduce child undernutrition in rural Burkina Faso and Kenya

**DOI:** 10.1186/s13063-022-06423-5

**Published:** 2022-06-01

**Keywords:** Evaluation, Stunting, Malaria, Bio-diversification, Behavioral change, Randomized controlled trial, Sub-Saharan Africa

## Abstract

**Background:**

Climate change heavily affects child nutritional status in sub-Saharan Africa. Agricultural and dietary diversification are promising tools to balance agricultural yield losses and nutrient deficits in crops. However, rigorous impact evaluation of such adaptation strategies is lacking. This project will determine the potential of an integrated home gardening and nutrition counseling program as one possible climate change adaptation strategy to improve child health in rural Burkina Faso and Kenya.

**Methods:**

Based on careful co-design with stakeholders and beneficiaries, we conduct a multi-center, cluster-randomized controlled trial with 2 × 600 households in North-Western Burkina Faso and in South-Eastern Kenya. We recruit households with children at the age of complementary feed introduction (6–24 months) and with access to water sources. The intervention comprises the bio-diversification of horticultural home gardens and nutritional health counseling, using the 7 Essential Nutrition Action messages by the World Health Organization. After 12-months of follow-up, we will determine the intervention effect on the primary health outcome height-for-age *z*-score, using multi-level mixed models in an intention-to-treat approach. Secondary outcomes comprise other anthropometric indices, iron and zinc status, dietary behavior, malaria indicators, and household socioeconomic status.

**Discussion:**

This project will establish the potential of a home gardening and nutrition counseling program to counteract climate change-related quantitative and qualitative agricultural losses, thereby improving the nutritional status among young children in rural sub-Saharan Africa.

**Trial registration:**

German Clinical Trials Register (DRKS) DRKS00019076. Registered on 27 July 2021.

## Administrative information

Note: the numbers in curly brackets in this protocol refer to SPIRIT checklist item numbers. The order of the items has been modified to group similar items (see http://www.equator-network.org/reporting-guidelines/spirit-2013-statement-defining-standard-protocol-items-for-clinical-trials/).

## Introduction

### Background and rationale {6a}

Climate change is likely to accelerate the prevalence of undernutrition among children in rural sub-Saharan Africa [1–3]. Today, chronic protein-energy undernutrition, defined as stunting, is seen among 32% of children aged < 5 years in West Africa and among 39% in East Africa [4]. Also, about one third of this vulnerable age group shows deficiencies in iron and zinc, respectively [5, 6].

Climate change is defined as “a change in the state of the climate that can be identified (e.g., by using statistical tests) by changes in the mean and/or the variability of its properties and that persists for an extended period, typically decades or longer” [7]. It is driven by greenhouse gas emissions, including fluorinated gasses, nitrous oxide (N_2_O), methane (CH_4_), and to a large proportion, carbon dioxide (CO_2_) [8]. Climate change manifests in sub-Saharan Africa through increased temperatures, higher rainfall variability, and more frequent weather extremes [9].

There are several biophysical and socio-economic pathways by which climate change impacts child undernutrition [10]. Primarily, climate change affects the nutritional status of children by compromising the availability, access, utilization, and stability of food supply [11]. Beyond the impacts on agricultural yields, increased atmospheric CO_2_ levels likely alter the content of essential nutrients in crops. As demonstrated by CO_2_ enrichment experiments in chambers and under open-field conditions (FACE), specific grains and tubers experience 7–17% protein losses and 3–11% reductions in zinc and iron [12, 13]. Based on the current trajectory of CO_2_ emissions consistent with achieving 550 parts per million (ppm) by roughly 2050, projections indicate that elevated atmospheric CO_2_ will cause an additional 122 million people to be protein deficient and an additional 175 million people to be zinc deficient [14]. These CO_2_ trends will also translate into > 4% of dietary iron losses for 1.4 billion people at increased risk of anemia worldwide, mainly women of childbearing age and children aged 6–59 months [14].

Diversifying the agricultural production of smallholder subsistence households constitutes one promising strategy to counteract the quantitative and qualitative harvest losses, thereby improving dietary diversity and nutritional status [15]. We define smallholder subsistence farmers as rural households with agricultural land use (max. 2 hectares (ha)), who rely on low-input and manual labor to produce the majority of their food [16, 17]. Subsistence farming families are characterized by low adaptive capacities and, therefore, require autonomous and planned adaptation to consolidate their food and nutrient supply [17, 18]. Indeed, agricultural and behavioral strategies are the main efforts in low- and middle-income countries (LMICs) to cope with the already existing impacts of climate change on human health [19]. Home gardening and nutrition counseling projects have been implemented to improve dietary diversity and child nutritional status in West Africa [20] and East Africa [21]. However, among 99 systematically reviewed studies on climate change adaptation in LMICs, only two have performed a priori evaluations of the responses to such adaptation strategies [19].

### Objectives {7}

The study title ALIMUS literately means “We are feeding.” The major goal of ALIMUS is to determine the effects of an integrated home gardening and nutrition counseling program on child nutritional status in rural Burkina Faso and Kenya. The specific objectives are to (i) establish the intervention effects on the primary outcome height-for-age *z*-score (HAZ) as a measure of chronic protein-energy undernutrition; (ii) determine the effects on secondary outcomes, including other anthropometric measures of undernutrition, iron and zinc status, dietary behavior, clinical malaria, and household socio-economic status; and (iii) identify the contributions of underlying impact pathways, comprising knowledge gains in horticultural practices and child feeding, and increased production of nutrient-rich fruits and vegetables.

A similar agricultural bio-diversification and nutrition counseling program was previously implemented by the non-governmental organization (NGO) Helen Keller International (HKI). This project was conducted and evaluated in Southern Burkina Faso [20, 22], but not in Kenya. Originally, HKI’s program aimed at improving mothers’ nutritional outcomes and empowerment through a set of agricultural production and nutrition interventions. The HKI program targeted mothers with children aged 3 to 12 months at baseline [23]. In contrast, ALIMUS targets the age when complementary foods are introduced to children (6 to 24 months). This acknowledges the age when stunting starts to develop among children, and accounts for the common practice of child fostering, meaning children being raised in households of relatives. The theory of change relies on three primary impact pathways (Fig. 1) to support the achievement of a healthy status of climate-sensitive nutrients among young children. These impact pathways are:Increased production of climate-resilient horticultural crops and diversification of crops for increased consumption of these foods;Increased knowledge related to the importance of agricultural diversification for the resilience of local crops and, thus, food and nutrient security for healthy families, thereby increasing the adoption of optimal practices; andIncreased output of the horticultural foods to increase income.

**Fig. 1 Fig1:**
[figure not shown]
Impact pathways of the integrated agricultural bio-diversification and nutrition counseling program, modified from Helen Keller International’s Homestead Food Production Program 2013

### Trial design {8}

The ALIMUS study is conducted as a multi-center, cluster-randomized controlled trial (RCT) with 300 households in the control group and 300 households in the intervention group at each study site. We perform baseline examinations of children at the age of complementary feed introduction (6–24 months) and follow-up these children for at least 1 year until the endline examinations. Baseline examinations take place in Burkina Faso between July and September 2021 and in Kenya between September and December 2021.

### Eligibility criteria {10}

In both study sites, the same eligibility criteria apply for participating households. A household is defined as “an independent socio-economic unit. Household members usually live in the same house or compound, pulling resources together to meet basic dietary and other vital needs under the authority of one person recognized as the head of the household” [25]. The eligibility criteria are as follows: location within a 5-km radius for Kenya and a 10-km radius for Burkina Faso of one of five local weather stations (Fig. 2), permanent residence in the HDSS area; access to at least 40 m^2^ land, access to water for implementing and sustaining a home garden, having a child at the age of supplementary feed introduction (6 to 24 months), and providing informed written consent by the caregiver.

**Fig. 2 Fig2:**
[figure not shown]
Map of the study villages in the Nouna Health and Demographic Surveillance System (HDSS), Burkina Faso (**A**) and the Kisumu HDSS, Kenya (**B**). Note: In the Kisumu HDSS, the villages are close together and, thus, separated by wider boundaries shown as polygons. All the villages located within the 5 km radii of the weather stations in the Kisumu HDSS are included in the study. In contrast, the villages in the Nouna HDSS, marked by black dots and blue diamonds, are widely spread; therefore, the weather stations cover a 10-km radii. Only some villages were randomly selected for inclusion in our study, which are marked with a blue diamond

### Who will take informed consent? {26a}

Prior to the program implementation, relevant authorities of the selected study villages (village chiefs and mayors) will be informed about the study aims and objectives by the Nouna CRSN and by the KEMRI-Kisumu. During the recruitment process, the participants will receive the participant information form, which will be read-out and explained to them. All questions will be answered by the project staff. All questionnaires, participant information forms, consent forms, and additional material will be made available in French for Burkina Faso and in English and Luo for Kenya. In addition, the interviewers will be trained to explain the content of the participant information forms in Djoula and Mooré in Burkina Faso and in Swahili in Kenya. All caregivers will give informed written consent.

### Additional consent provisions for collection and use of participant data and biological specimens {26b}

These items are part of the original consent form. This trial does not involve collecting biological specimens for storage.

### Interventions

#### Explanation for the choice of comparators {6b}

For the allocation of intervention arms, we apply simple randomization, treating the households as intervention clusters. At each site, the main data manager of the baseline survey produces a computer-generated sequence of households that are allocated to either the intervention group or the control group, applying the PPS approach. The implementation partners for home gardens (DEZLY Consulting, the Nouna Agricultural Service and CABE) and the lead dieticians for nutrition counseling use these lists of randomized households to implement the intervention components. As this is a behavior change trial, blinding the participants and or the implementation team is not possible.

All participating households in the ALIMUS trial benefit from trimonthly follow-up visits by a research study team (not Community Health Volunteers (CHVs). During these follow-up visits, the study team takes anthropometric measures and examines iron and zinc status of the target child. We also assess signs and symptoms of clinical malaria and provide diagnostic tests if a child has fever, shivers, a headache, or diarrhea. In case of sickness, the child and the caregiver are referred to the nearest health care facility for appropriate treatment. For the control group, we provide standard information on healthy feeding practices. This comprises one group counseling session on the Essential Nutrition Action (ENA) messages, but no tailored individual sessions afterwards. During the group counseling, we hand-out an information leaflet corresponding to the ENA messages.

#### Intervention description {11a}

The intervention program has two components: bio-diversification by means of home gardens and dietary diversification through behavior change communication. The intervention period will last for at least 1 year.

For the home garden component, we apply the following definition. Home gardens are small plots (< 40 m^2^) located near the house for growing vegetables and/or fruits, primarily for the household’s own food consumption. For home garden implementation, we collaborate with three experienced local partner organizations. In Burkina Faso, we work with DEZLY Consulting, a consulting service organization (CSO), and the Nouna Agricultural Service, and in Kenya, we collaborate with the NGO Centre for African Bio-Entrepreneurship (CABE). The intervention activities by partner organizations comprise sensitization of community members, distributing inputs, and providing training to garden leaders. These garden leaders come from the participating communities with one garden leader being responsible for approximately 20 beneficiary households. They have experience in home gardening, are respected members of their communities, have independent means of transportation, and are committed to working as volunteers in this project. In two phases, garden leaders are trained by DEZLY Consulting and the Nouna Agricultural Service in Burkina Faso and by CABE in Kenya on theoretical and practical aspects of home gardening. The first phase (months 1 to 3) focuses on the establishment of the home gardens, while the second phase (months 9 to 12) concentrates on the long-term viability of the gardens and a potential market access through garden produce surplus. The training elements comprise the selection of garden types and horticultural crops, marking and fencing the gardens, seed production and multiplication, methods of manure creation and composting, soil preparation, weeding and plant protection, harvesting, and food storage. We purposefully employ only climate-friendly and durable inputs and processes, such as local products for fencing and construction, participatory selection of indigenous crops that meet the beneficiaries’ preferences and are not genetically engineered. We also exclusively collaborate with regional seed providers and use organic pesticides and fertilizers. For refresher trainings and trouble-shooting, two extension officers per study site will be appointed by DEZLY Consulting in collaboration with the local Agricultural Service in Burkina Faso, and by CABE in Kenya.

In regard to the behavior change communication component, at each study site, one formally trained dietician is responsible for training and supervising CHVs. Each CHV provides nutrition counseling to about 20 households at each study site. CHVs are members of their communities appointed by the local authorities of the Ministry of Health. They have minimal training in maternal and child health or nursing and are of the same ethnic background as the ALIMUS beneficiaries. Half of the CHVs are males. The content of the nutrition counseling is sourced from the 7 ENA messages by the World Health Organization (WHO) [32]. These ENA messages are implemented in the form of the Infant and Young Child Feeding (IYCF) Cards by the Ministries of Health in Burkina Faso and Kenya. The 7 ENA messages comprise the following: (1) children’s nutritional needs (calories, protein, micronutrients), (2) breastfeeding practices, (3) complementary feeding practices, (4) nutritional care for sick and severely malnourished children, (5) prevention and control of anemia (zinc, iron), (6) prevention and control of vitamin A deficiency, and (7) prevention and control of iodine deficiency.

Nutrition counseling is provided to the beneficiaries in group sessions at the beginning of the intervention and during individual sessions in the beneficiaries’ household every 2 months. Just as the different IYCF Cards target different age groups, the individual nutrition counseling sessions are also tailored to the feeding stages of the target child.

#### Criteria for discontinuing or modifying allocated interventions {11b}

The project team closely collaborates with the local Ministries of Agriculture and Ministries of Health. In case we will observe clinically relevant improvements in the nutritional status after 1 year of the intervention, we will seek their support for offering the program to the control households, too.

#### Strategies to improve adherence to interventions {11c}

Adherence to the intervention will be supported through regular contacts to the beneficiaries during training sessions on home gardening and individual nutrition counseling. We will closely monitor the uptake of inputs such as seeds and garden tools, as well as the participation in all sessions.

#### Relevant concomitant care permitted or prohibited during the trial {11d}

No concomitant care prohibited.

#### Provisions for post-trial care {30}

No provision of post-trial care.

#### Outcomes {12}

The ALIMUS trial targets as the primary outcome the height-for-age z-score (HAZ) of the target children after 12 months of follow-up according to the 2006 WHO Child Growth Standards [33]. Secondary outcomes comprise additional anthropometric *z*-scores (weight-for-height (WHZ) and weight-for-age (WAZ)) after the 12 months intervention period; measures of dietary behavior at endline, including energy intake, consumption of macronutrients and micronutrients, food group intakes, indices of dietary diversity, and exploratory dietary patterns; the nutritional status of iron and zinc measured by hand-held spectrometry at endline; the incidence of clinical malaria; and the socio-economic status of the household.

#### Participant timeline {13}

At both study sites, each participant is followed-up for at least 1 year, with a possible extension of an additional year (Table 1). After community sensitization, eligibility screening and consent taking, we perform baseline examinations over the course of 3 months. We then randomize households and allocate them to either the intervention group (*n* = 300 at each site) or the control group (*n* = 300 at each site). In groups of 20 beneficiaries, the intervention group participants receive trainings in setting up their gardens by their respective garden leader and counseling sessions on healthy child feeding practices by CHVs. Every 2 months, garden leaders and CHVs actively visit the intervention households for guidance on home garden practices and individual dietary counseling. In 3 month intervals, we integrate anthropometric measurements and assessments of micronutrient status and clinical malaria into this schedule. After the first 6 months of the intervention, refresher trainings of the beneficiaries for home garden practices are conducted in the form of group sessions. After another 6 months (1 year since start), we conduct endline examinations for the primary and secondary outcomes among all study participants. In addition, we monitor inputs and outputs according to the three major impact pathways throughout the intervention phase.

**Table 1 Tab1:** Activity timeline for the ALIMUS trial in rural Burkina Faso and Kenya

Time point	2021						2022												2023			
	Q3			Q4			Q1			Q2			Q3			Q4			Q1			Q2
**Enrolment**																						
Eligibility screening of study participants	X	X																				
Community sensitization and informed consent	X	X																				
Recruitment of study participants			X	X	X																	
Randomization and allocation					X																	
**Intervention**																						
Training of garden leaders and CHVs			X	X	X																	
Nutrition counseling																						
Group counseling (1 session only)							X	X														
Bi-monthly individual counseling sessions^a^									X	X	X	X	X	X	X	X	X	X				
Home garden training^a^																						
Organic pesticide and manure production							X	X							X							
Composting and nursery establishment							X	X							X							
Land preparation, construction and planting								X	X							X						
Weeding and plant protection									X	X						X						
Harvesting, value addition and storage										X	X						X					
Training on maintenance of home gardens												X	X	X								
**Monitoring**																						
Input monitoring (cont.)		X		X			X			X			X			X			X			
Knowledge gains																			X			
Species richness and garden yields (cont.)							X			X			X			X						
**Assessments**																						
Interviews on diet, demographics, socio-economic status		X		X	X														X	X	X	
Anthropometric examinations		X		X	X														X	X	X	
Micronutrient measurements, 3-monthly^b^									X			X			X			X			X	
Malaria assessments, 3-monthly^b^									X			X			X			X			X	
**Evaluation**																						
Cross-sectional baseline analysis				X			X															
Intention-to-treat and differences-in-differences analyses																				X	X	X

^a^Only for the intervention groups

^b^Only in Kenya

#### Sample size {14}

In order to identify the required sample size for this RCT, we referred to the parallel group- or cluster-randomized trials (GRT) Sample Size Calculator of the USA National Institutes of Health (NIH) (https://researchmethodsresources.nih.gov/). The sample size was calculated based on the primary outcome child HAZ, assuming a group difference in mean HAZ ranging between 0.18 to 0.25. At a significance level of 0.05, a statistical power of 80%, an intra-class correlation coefficient (ICC) of 0.05, and with 2 children per household (=cluster), the sample size ranges from 135 households (difference in mean HAZ of 0.25) to 260 households (difference in mean HAZ of 0.18). Therefore, at each study site, we set the sample size to 300 households in the intervention group and 300 households in the control group, accounting for potential attrition and loss to follow-up. This sample size will allow the detection of a difference in the incidence of clinical malaria of 0.16 standard deviation (SD), under the same assumptions.

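### The sample size assumes two children per household, but the design described follows one target child, so 80% power per site at a HAZ difference of 0.18 is not supported

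*Protocol article*

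**What the plan says.** Protocol article, Sample size {14}: the calculation is for child HAZ, "assuming a group difference in mean HAZ ranging between 0.18 to 0.25". The other inputs are a 5% significance level, 80% power and an ICC of 0.05. The household numbers are given as follows: "and with 2 children per household (=cluster), the sample size ranges from 135 households" for the larger difference, rising to 260 for the smaller one. From this the section sets 300 households per arm at each site, with the excess covering attrition. It then adds: "This sample size will allow the detection of a difference in the incidence of clinical malaria of 0.16 standard deviation (SD"), and says that this uses the HAZ assumptions. The SD of HAZ is not given.

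Other sections describe the child side of the design in the singular:

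- Eligibility criteria {10}: a household qualifies by "having a child at the age of supplementary feed introduction (6 to 24 months").
- Explanation for the choice of comparators {6b}: at follow-up visits "the study team takes anthropometric measures and examines iron and zinc status of the target child".
- Intervention description {11a}: individual counselling is fitted to the feeding stage of the target child, again singular.
- Outcomes {12}: the primary outcome is HAZ of the target children after 12 months. This plural runs across households and does not say how many come from each.

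Statistical methods {20a} stratifies the intervention effects by study site, so each site's estimate rests on its own 300 + 300 households.

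**The concern.** The number of children per household drives the calculation. At an ICC of 0.05, a second child in the household adds almost a full extra observation, so moving from two children to one nearly halves the information. The sample size section counts 600 children per arm per site, while the design described elsewhere yields about 300.

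The protocol presents each site as having 80% power down to a HAZ difference of 0.18, with attrition covered. If the number of children is nearer one per household, a null result at one site could be taken as evidence against a 0.18 effect when the site had a substantial chance of missing it. The malaria statement has the same weakness because it uses the same assumptions.

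**Working it through.** **Inputs.** From Sample size {14}: significance level 0.05, power 80%, ICC ρ = 0.05, m = 2 children per household, differences δ of 0.18 and 0.25, and 300 households per arm per site. Assumed: SD = 1 (not stated) and a two-sided test (sidedness not stated). The value 260 per arm is used as a second case because the protocol gives it as the requirement at 0.18. It would correspond to losing 40 of 300 (13%), although no attrition rate is stated.

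**Step 1: reproduce the stated figures.** Households per arm = 2 × (1.960 + 0.842)² / δ² × [1 + (m − 1)ρ] / m.

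- δ = 0.25, m = 2: 251.2 × 1.05 / 2 = 131.9, so 132 (stated 135).
- δ = 0.18, m = 2: 484.5 × 1.05 / 2 = 254.4, so 255 (stated 260).

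Both are within 3%. The stated numbers are therefore households per arm, two-sided, with SD 1. A one-sided test gives 104 and 201, which does not match. With m = 1 the same formula gives 252 and 485.

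**Step 2: power by children per household.** Effective children per arm: n = K·m / [1 + (m − 1)ρ], where K is households per arm. Power = Φ(δ / √(2/n) − 1.96).

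For m = 1 the design effect is 1 and the ICC plays no part:

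- K = 300, δ = 0.18: 0.18 / 0.0816 − 1.96 = 0.245, power 59.7%.
- K = 260, δ = 0.18: 0.18 / 0.0877 − 1.96 = 0.092, power 53.7%.

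| Average children per household | Power at 0.18, K = 300 | Power at 0.18, K = 260 |
|---|---|---|
| 1 | 59.7% | 53.7% |
| 1.3 | 70% | 64% |
| 2 | 86.1% | 80.9% |

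For m = 1.3, n = 390 / 1.015 = 384 (K = 300) and 338 / 1.015 = 333 (K = 260).

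**Step 3: detectable difference and the other end of the range, m = 1.** The 80% detectable difference is 2.8016 × √(2/K), which is 0.229 for K = 300 and 0.246 for K = 260. Power at 0.25 is 86.5% (K = 300) and 81.3% (K = 260).

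**Step 4: average needed for 80% power at 0.18.** Solve K·m / (0.95 + 0.05m) = 484.5. This gives m = 1.67 for K = 300 and m = 1.95 for K = 260.

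**Step 5: malaria figure.** By the same two-means formula, 600 children per arm with design effect 1.05 gives 2.8016 × √(2 × 1.05 / 600) = 0.166 SD. Without the design effect it is 0.162. With 300 children per arm it is 0.229. This is approximate, since Statistical methods {20a} analyses malaria incidence by negative binomial regression.

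**Sensitivity to assumptions (m = 1, δ = 0.18, K = 260 to 300).** An SD of 1.2 lowers power to 40–45%. Adjustment for baseline HAZ multiplies the residual SD by √(1 − r²): power is 73–79% at a baseline–endline correlation r of 0.6 and 82–87% at r = 0.7. The protocol gives no value for r.

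**The case against.** The strongest reply is that no sentence limits enrolment to one child. The eligibility wording sets a minimum for the household to qualify. Recruitment {15} speaks of households with children in the plural. Statistical methods {20a} plans a multi-level model and compares baseline on separate household and participant levels. The trial calls the household a cluster, and the sample size section itself says two. The household definition covers compounds, Objectives {7} mentions child fostering, and Study setting {9} gives 115,000 / 14,000 = 8.2 people per household in Nouna against 220,000 / 54,869 = 4.0 in Siaya. An average above one is credible, and it may differ between sites.

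This stands in part. A reader might infer that the protocol fixes one child per household, so that true power is 54–60%. The documents do not support that: one child is the consistent reading of the singular wording, not a stated rule, and 54–60% also depends on SD 1 and no baseline adjustment. The reply does not rescue the 80% claim at 0.18, however. That needs an average of roughly 1.7 to 2.0 children within an 18-month age window, and nothing outside the sample size section points to such an average.

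A second reply is that adjustment and difference-in-differences analyses are planned and could recover power. They could, but the sample size section does not rely on them, baseline HAZ is not named as a covariate, and no correlation is given.

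**Conclusion.** The point holds as an inconsistent input. The arithmetic itself is sound, since the plan's own figures reproduce closely. The 80% power per site at a HAZ difference of 0.18 depends on two measured children per household, which the described design does not provide for.

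The one-child figures of about 60% (300 per arm) and 54% (260 per arm) are conditional on one child, SD 1 and an unadjusted endline comparison. An average of 1.3 children gives 64–70%.

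The shortfall is confined to the lower part of the effect range. It would be wrong to infer that the trial is underpowered throughout, because one child per household still gives 81–86% at 0.25. The lower end matters because it produced the 260 from which 300 was chosen.

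Nor does the point oblige the trial to make a pooled two-site estimate its primary test. That would replace the site-stratified analysis in Statistical methods {20a} and is not needed to correct the power statement.

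**What to change.** - Reconcile Sample size {14} with Eligibility criteria {10}, Explanation for the choice of comparators {6b}, Intervention description {11a} and Outcomes {12}, by stating how many children per household were enrolled at each site. Trial status reports recruitment and baseline complete as of January 2022, so the number is known.
- State the SD of HAZ used.
- Restate the per-site power at 0.18 and 0.25, and the 80% detectable difference, on the actual number of children. Do not enrol more.
- Recompute the malaria figure on the same basis. With 300 children per arm it is about 0.23 SD by the two-means formula, to be labelled approximate given the negative binomial analysis.
- If credit is taken for baseline-HAZ adjustment, give it as a separate line with the assumed correlation.
- A pooled two-site estimate may be added as a supplementary analysis.

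The cost is a change of wording and a short recalculation. The downside is a less favourable per-site power statement if the average number of children is well below two.
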